**Fig. 5 Fig5:**
[figure not shown]
Flow diagram for planned recruitment and differentiation of study arms

Inclusion criteria at the cluster level (LTCF) and within clusters are described in Table 1. Within each cluster, all eligible participants (INTERCARE nurses, residents, staff, physicians, and LTCF leadership) who meet the inclusion criteria will be included.

**Table 1 Tab1:** Inclusion and exclusion criteria

**Staff** **(expected number of participants)**	**Inclusion criteria**	**Exclusion criteria**
LTCFs (cluster level)	• German-speaking • ≥20 long-term care beds • Cantonal accreditation • Formal commitment to introduce the INTERCARE core components • Willingness to provide routine resident assessment data	• Already working with INTERCARE nurses and existing high fidelity to INTERCARE core elements
INTERCARE nurse (1–3 per LTCF)	• Employment or formal affiliation with the LTCF • At least a registered nurse degree and three years’ experience working with older adults • Formal assignment as an INTERCARE nurse	• Temporary substitute of INTERCARE nurse (e.g., during holidays)
Residents (ca. 4,000 in total)	• All residents present during the study period who are billed under the health insurance law	• Opt-out by residents or their legal representative • Short-stay residents
Care staff (ca. 3,200 in total)	• All direct care staff (e.g., care workers, physiotherapists, activity staff) at different educational levels (RNs, licensed practical nurses, nurse aides) who work ≥8 hours/week for ≥3 months • Therapeutic personnel involved in treatments ≥8 hours/week	• Non-healthcare professionals (e.g., administrative staff)
General Practitioner (GP) (ca. 400 in total)	• Treating at least five residents in the LTCF at the time of the survey	• Temporary substitute GPs
LTCF leadership (ca. 80 in total)	• LTCF director, director of nursing, project manager (if different), relevant unit leaders, and other designated personnel (e.g., quality manager, needs assessment instrument supervisors)	• Leadership person not involved in the study

### Randomization

Allocation of LTCFs to each arm will be concealed from recruiters in the project team. A project collaborator not involved in recruitment will use computer-generated random numbers to allocate LTCFs (simple randomization) after LTCFs have signed the formal commitment and consented to participate [57]. Allocation will remain concealed from LTCFs, staff, and the research team until all LTCFs in the cohort are assigned; thereafter, both researchers and LTCFs will be aware of the allocation. The timing of cohort assignment and implementation start will be discussed with LTCFs based on their self-reported readiness to implement and their appointment of an INTERCARE nurse.

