**Methods:**

This non-inferiority, effectiveness–implementation hybrid type III trial uses a cluster-randomized controlled design, with LTCFs as the unit of randomization. Forty German-speaking LTCFs in Switzerland (≥20 long-term care beds; cantonal accreditation) will be randomized (1:1) after formal consent to either individualized or collective implementation support, without blinding of LTCFs or the research team. In the individualized arm (20 LTCFs), leadership receives 1:1 support meetings, and INTERCARE nurses receive 1:1 coaching, mirroring the original INTERCARE trial. In the collective arm (20 LTCFs), leadership support and INTERCARE nurse coaching are delivered in group formats involving several LTCFs/INTERCARE nurses together at two-monthly intervals. The primary outcome is LTCF-level fidelity to the INTERCARE core components, analyzed with a binomial generalized linear mixed model including a random LTCF effect. Non-inferiority of the collective mode will be concluded if the lower bound of its 95% confidence interval for fidelity is within 15% of the individualized mode. A 12-month cost-effectiveness analysis from a multi-stakeholder perspective (LTCFs and research group) will estimate the incremental cost-effectiveness ratio using differences in implementation costs and unplanned transfers between arms; secondary outcomes include unplanned transfers, staff turnover, and absences.

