### Sample size and inclusion criteria

LTCFs will be recruited via LTC national and professional associations, magazines, direct contact, and snowballing. The sample size calculation assumes a 15% difference in overall fidelity between trial arms (65% vs. 80%). Based on a simulation with 2,000 iterations, a between-cluster variance of 0.1 (ICC = 0.029), and a two-sided alpha of 0.025, 18 LTCFs per arm provide 84% power to detect a 15% difference; for a 20% difference, power increases to 97%. Allowing for a 10% loss between consent and allocation, and after intervention start, the target sample is 40 LTCFs (20 per arm) (Fig. 5).

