### Implementation strategies, mode of delivery, and study arms

In WP1, implementation strategies were specified and differentiated between the two study arms (Fig. 3). Strategies target LTCF model implementers, LTCF leadership (e.g., LTCF director, director of nursing), and INTERCARE nurses and are fully described using the AACTT framework [50] in Supplementary Material 2.

The key contrast between arms is the mode of delivery of support meetings for LTCF model implementers and coaching for INTERCARE nurses. In arm I (individualized support), support meetings with LTCF model implementers and coaching sessions with INTERCARE nurses are held separately for each LTCF and for each INTERCARE nurse, respectively. In arm II (collaborative support), LTCF model implementers and INTERCARE nurses are grouped across LTCFs within the same cohort arm for joint support and coaching sessions.

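### Simple randomization does not guarantee 20 LTCFs per arm, or enough arm II LTCFs in each cohort to form the support group the design needs

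*Protocol article*

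**What the plan says.** The Randomization section of the protocol article names the method: a collaborator not involved in recruitment "will use computer-generated random numbers to allocate LTCFs (simple randomization"). Allocation runs by cohort and is withheld "until all LTCFs in the cohort are assigned". When a cohort is assigned and starts is agreed with the LTCFs, depending on how ready they report themselves to be and whether an INTERCARE nurse has been appointed.

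Three other statements depend on how that allocation turns out:

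- The abstract says that LTCFs "will be randomized (1:1) after formal consent to either individualized or collective implementation support" and puts 20 LTCFs in each arm.
- Sample size and inclusion criteria: "the target sample is 40 LTCFs (20 per arm"), reached from 18 per arm with an allowance of 10% for loss.
- Implementation strategies, mode of delivery, and study arms: in arm II, model implementers and nurses are "grouped across LTCFs within the same cohort arm for joint support and coaching sessions". The abstract describes this support as "delivered in group formats involving several LTCFs/INTERCARE nurses together at two-monthly intervals".

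The text gives no block, stratum, fixed arm total, cohort size or minimum group size.

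**The concern.** Under simple randomization each LTCF is in effect allocated by its own coin toss. Arm sizes are then random, both overall and within each cohort. The design relies on both: overall for the planned 20 per arm, and within cohorts because an arm II group can be drawn only from LTCFs in the same cohort arm.

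The second dependence matters more. A cohort with no arm II LTCF has no group. A cohort with one has an LTCF that cannot receive support jointly with others as the article defines it. The article does not say what would then happen. If that LTCF were supported alone, its treatment would resemble arm I. The mode of delivery is the contrast under test, and in a non-inferiority trial a diluted contrast tends to favour a conclusion of non-inferiority.

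A lesser cost is chance imbalance between arms in cohort, and so in readiness and start time. Readiness plausibly relates to fidelity, so this is noise in the primary comparison that the design could remove.

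**Working it through.** **1. The plan's own figures.**
- Inflation for loss: 18 / (1 − 0.10) = 20 per arm, 40 in total. This agrees with the article.
- ICC on the logit scale: 0.1 / (0.1 + π²/3) = 0.0295, against 0.029 stated.
- Power: the number of minimal requirements per LTCF, m, is not in the text, so it is assumed. The check simulated logit-normal clusters with variance 0.1, 65% vs 80%, two-sided alpha 0.025, and a Wald test on cluster proportions as an approximation to the mixed model. At 18:18 this gives 82% for m = 12, 84% for m = 13 and 87% for m = 14. The stated 84% is reproduced at m = 13.

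**2. Overall arm sizes.** The size X of one arm is Binomial(40, 0.5), with standard deviation √(40 × 0.25) = 3.16.
- P(X = 20) = C(40,20)/2⁴⁰ = 12.5%.
- P(X = 19) = P(X = 21) = 11.9%; P(X = 18) = P(X = 22) = 10.3%.
- P(18 ≤ X ≤ 22) = 12.5 + 2 × 11.9 + 2 × 10.3 = 57.0% (unrounded terms).
- P(smaller arm below 18) = 100 − 57.0 = 43.0%, before any LTCF is lost.

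**3. What unequal arms cost in power** (m = 13, 36 evaluable LTCFs).
- 18:18 gives 84%.
- 15:21 gives 82–84%, depending on which arm is smaller.
- 12:24 gives 77–81%.
- Averaged over the random split, power is 83%.

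**4. Arm II LTCFs within a cohort.** For a cohort of k, the arm II count is Binomial(k, 0.5), so p = P(0 or 1) = (1 + k)/2ᵏ. With 40/k cohorts, P(at least one such cohort) = 1 − (1 − p)^(40/k). Cohort size is an assumption throughout.

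| k (assumed) | Cohorts | p per cohort | At least one such cohort |
|---|---|---|---|
| 4 | 10 | 5/16 = 31.3% | 98% |
| 5 | 8 | 6/32 = 18.8% | 81% |
| 8 | 5 | 9/256 = 3.5% | 16% |
| 10 | 4 | 11/1,024 = 1.1% | 4% |
| 20 | 2 | 21/1,048,576 = 0.002% | about 0 |

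If a group needs at least three LTCFs (also an assumption), the per-cohort chance of 2 or fewer is 50% for k = 5, 14.5% for k = 8 and 5.5% for k = 10. The chance of at least one short cohort is then 99.6%, 54% and 20%.

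**5. After exact 1:1 allocation within cohort.** Each cohort has at least ⌊k/2⌋ LTCFs in arm II: 2 of 4, 2 of 5, 4 of 8, 5 of 10. Even-sized cohorts give exactly 20:20. With eight cohorts of 5, each rounded at random, an arm has 16 + Binomial(8, 0.5) LTCFs. Its standard deviation is √(8 × 0.25) = 1.41 instead of 3.16.

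**The case against.** The other side has several fair points.

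- *A 1:1 ratio is met in expectation, and 20 per arm is called a target.* True. The method can produce the planned split but does not guarantee it.
- *Power hardly changes.* True, and it limits the point. A reader might infer from the 43% figure that the trial is likely to be underpowered. Step 3 does not support that: the average loss is about one percentage point.
- *Allocation is random and concealed until the cohort is complete.* True. A reader might infer that arm is confounded with readiness or calendar time. It is not: any imbalance is due to chance and costs precision, without systematic bias.
- *The missing cohort term is not an error.* True. The article states no stratification, and an article commonly leaves covariates to the analysis plan. A cohort term is called for only because the proposed fix makes cohort a stratification factor.
- *The deliverability risk depends on a cohort size the text does not give.* True. Figures 4 and 5 and Supplementary Material 2 were not available for this check and may give it. With cohorts of 20 the risk is negligible, and nothing in the text singles out small cohorts.
- *Exact 1:1 within small cohorts may still give groups that are too small.* True. A cohort of 5 can have two arm II LTCFs, and one dropout leaves one. The fix must therefore also address cohort size.

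What remains is a stated method that does not secure what other sections rely on. It cannot be set aside as detail left to a fuller document, because the article names simple randomization explicitly.

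**Conclusion.** The point holds as a cheap design improvement and does not invalidate the trial. Simple randomization leaves both the overall split and the arm II count in each cohort to chance. The overall figures (12.5% for exact balance, 43% for a smaller arm below 18) assume only that 40 LTCFs are allocated independently with probability one half. Their consequence for power is slight, about 84% to 83%, and rests on the assumed 13 requirements per LTCF.

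The consequence that matters is whether arm II can be delivered as described. The chance that at least one cohort has fewer than two arm II LTCFs runs from 98% for cohorts of 4 to about 0 for cohorts of 20. It is serious for cohorts of 4 or 5, still material at 8, and minor at 10 or more. A reader might conclude that the collaborative arm will fail in some cohorts. Without a stated cohort size, the documents show only that it can.

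**What to change.** For cohorts not yet randomized:

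1. Keep the computer-generated, concealed process, but allocate each cohort as one batch at exact 1:1, with odd-sized cohorts rounded at random. Even-sized cohorts are preferable because they give 20:20 exactly.
2. Make each cohort large enough for its arm II half to form a group, allowing for dropout, and state the minimum group size.
3. Include cohort in the primary model, since it becomes a stratification factor.

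If restricted allocation is already used, correct the Randomization section to say so. For cohorts already randomized, report the number of LTCFs by cohort and arm.

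The cost is a change to the allocation script and, for the cohort term, one degree of freedom fewer than the number of cohorts. Larger cohorts may mean that some LTCFs wait longer to start. Batch allocation adds no practical predictability, because assignments are already withheld until the whole cohort has been assigned.

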### Intervention

The intervention is the INTERCARE nurse-led care model with six core components (INTERCARE nurse, interprofessional collaboration, advance care planning, evidence-based communication tools, comprehensive geriatric assessment, and data-driven quality improvement), as detailed in Supplement 1 and the previous INTERCARE protocol [58]. For each core component, minimal requirements – deemed essential for effectiveness – must be introduced (e.g., ACP conversation with each newly admitted resident). These minimal requirements were refined in WP1 to align with updated evidence and context.

To support implementation, performance objectives are defined for each minimal requirement (e.g., the INTERCARE nurse, together with their supervisors and the unit leaders, develops a work plan that outlines designated time slots for regular exchanges with each unit). Peripheral elements beyond minimal requirements describe acceptable variants (e.g., job-sharing for INTERCARE nurses), which LTCFs may adopt as appropriate.

### Implementation strategies, mode of delivery, and study arms

In WP1, implementation strategies were specified and differentiated between the two study arms (Fig. 3). Strategies target LTCF model implementers, LTCF leadership (e.g., LTCF director, director of nursing), and INTERCARE nurses and are fully described using the AACTT framework [50] in Supplementary Material 2.

The key contrast between arms is the mode of delivery of support meetings for LTCF model implementers and coaching for INTERCARE nurses. In arm I (individualized support), support meetings with LTCF model implementers and coaching sessions with INTERCARE nurses are held separately for each LTCF and for each INTERCARE nurse, respectively. In arm II (collaborative support), LTCF model implementers and INTERCARE nurses are grouped across LTCFs within the same cohort arm for joint support and coaching sessions.

### Data collection

Data are collected at baseline and then every three months during the implementation and sustainment phases (Fig. 4). Data sources include online surveys, structured reports, semi-structured interviews, observations, Excel data sheets, and the extraction of routine data and staff rosters for implementation, economic, and effectiveness outcomes (Table 2).

**Table 2 Tab2:** Data collection points in view of study aims and target population

				**Intervention phase**				**Sustainment phase**			
	**Target population**	**Data source**^**a**^	**T0**	**T1**	**T2**	**T3**	**T4**	**T5**	**T6**	**T7**	**T8**
**Implementation outcome**											
Overall fidelity score (intervention phase) (aim 1)	LTCF leadership	Semi-structured interview (quan. and qual. data)	x	x	x	x	x				
Fidelity to core components (aim 2.1):											
a) Interprofessional collaboration	INTERCARE nurse, LTCF staff	Online survey	x		x		x				
	Physicians				x		x				
b) INTERCARE nurse	INTERCARE nurse	Structure report about coaching activities (qual. data)		x	x	x	x	x	x	x	x
		Observations (qual. data)			x						
c) Comprehensive Geriatric Assessment	LTCF leadership	Structure report about activities related to CGA (qual. data)					x				
d) Evidence-based tools	LTCF staff	Online survey	x		x		x				
	Physicians				x		x				
e) Advance Care Planning	Residents (reported by LTCF leadership/INTERCARE nurse)	Excel data sheet	x	x	x	x	x	x	x	x	x
f) Data-driven quality improvement	LTCF leadership/project team	Structured report about activities related to data-driven quality improvement (qual. data)					x				
Sustainability (aim 2.1)	LTCF leadership	Semi-structured interview (quan. and qual. data)						x	x	x	x
Acceptability (aim 2.1)	LTCF leadership (only T0 and T4), INTERCARE nurse, LTCF staff	Online survey	x		x		x				
Feasibility (aim 2.1)	LTCF leadership (only T0 and T4), INTERCARE nurse, LTCF staff	Online survey	x		x		x				
**Economic outcomes**											
Costs of implementation strategies (aim 2.2)	LTCF leadership, staff involved in implementing INTERCARE; INTERSCALE research team	Online form	x	x	x	x	x	x	x	x	x
Wages, price list and transfer’s impact on LTCF revenues (aim 2.2)	LTCF leadership	Questionnaire		x				x			x
**Effectiveness outcomes**											
Unplanned transfers (aim 2.3a)	Residents (reported by LTCF leadership/INTERCARE nurse)	Excel-based quality monitoring tool	x	x	x	x	x	x	x	x	x
Staff turnover (aim 2.3b)	LTCF leadership	LTCF routine data/exports from staff rosters	x	x	x	x	x	x	x	x	x
Staff absences (aim 2.3b)	LTCF leadership	LTCF routine data/exports from staff rosters	x	x	x	x	x	x	x	x	x
Staff intent to leave (aim 2.3b)	LTCF staff	Online survey	x		x		x				

T0 to T8 refer to timepoints from baseline (T0) to start of intervention (T1, one month after T0) followed by three-monthly data collection points (T2 to T8)

*Abbreviations*: *LTCF* long-term care facility

^a^ Data is quantitative unless otherwise marked

#### Implementation outcomes (aims 1 and 2.1)

Overall fidelity to INTERCARE core components (primary outcome, aim 1) will be assessed via semi-structured interviews with LTCF leadership every three months. Two researchers (one interviewer, one note-taker) will review each minimal requirement and classify it as systematically, partially, or not (yet) implemented, yielding an overall fidelity score (percentage of minimal requirements implemented as intended) at each time point. Fidelity will be interpreted as high (80–100%), moderate (51–79%), or low (0–50%), following published cut-offs [59, 60].

For aim 2.1, fidelity will also be measured separately for each core component using: 1) online surveys of INTERCARE nurses, LTCF staff, and physicians (interprofessional collaboration and evidence-based tools); 2) structured reports from LTCF leadership (comprehensive geriatric assessment and data-driven quality improvement); 3) structured reports and observation of INTERCARE nurses’ coaching activities; 4) and Excel data sheets reporting ACP conversations with newly admitted residents, at time points defined in Table 2. Sustainability will be assessed by overall self-reported fidelity over 12 months post-implementation.

Acceptability and feasibility of selected core components will be assessed with the Acceptability of Intervention Measure (AIM) and Feasibility of Intervention Measure (FIM) [61]. INTERCARE nurses and LTCF staff will complete online surveys at T0, as well as 6 and 12 months after intervention start (T2, T4), while leadership will be surveyed at T0 and T4 (cf. Table 2).

#### Economic outcomes (aim 2.2)

Costs and cost-effectiveness will be assessed from LTCF and research group perspectives using a multi-stakeholder approach [62]. Time-driven activity-based costing (TDABC) [63] will be applied during implementation and sustainment phases. Structured REDCap [64] forms will capture time spent on each implementation activity (what was done, by whom, and for how long), separately asking for the hourly wage to calculate costs per hour for the human resources used. The structured forms will be completed by LTCF personnel (including leadership, INTERCARE nurses, and other local staff targeted by the implementation strategies) and the research group. Each LTCF will provide its service price list and information on the financial impact of hospital transfers and potentially empty LTCF beds. Cost data will be merged to estimate total intervention and implementation costs. Combined with effectiveness data on unplanned hospital transfers (aim 2.3), these will be used to calculate the incremental cost-effectiveness ratio (ICER).

#### Effectiveness and organizational outcomes (aims 2.3a, 2.3b)

The clinical outcome is the number of unplanned transfers at resident level, defined as any unscheduled transfer to the ED or hospital; planned transfers (e.g., follow-up appointments, non-emergency surgery) will be excluded [65]. LTCFs will use an Excel-based monitoring tool to track hospitalizations (admission and discharge dates, type of visit, length of stay, reason for transfer). The main indicator will be unplanned transfers per 1,000 care days, with sub-analyses separating ED visits and hospital stays; only fully anonymized data will be provided to the research team.

Organizational outcomes include staff absences (sick days relative to working days and proportion of staff with sick days) and staff turnover (monthly proportion of staff who left), assessed over time. At staff level, intention to stay and intention to leave will be measured via online surveys, and facility, socio-demographic, and professional characteristics will be collected for LTCFs, LTCF leadership, INTERCARE nurses, staff, and physicians to describe the samples.

#### Qualitative data (aim 2.1)

Qualitative data will focus on fidelity to the INTERCARE nurse core component, specifically the minimum requirement “The INTERCARE nurse coaches the teams concerning complex resident situations and acute situations,” as this is a key ingredient for successful reduction in unplanned transfers, based on the INTERCARE process evaluation [66]. An insider (emic) perspective will be captured through fidelity interviews with leadership and INTERCARE nurses. In addition, INTERCARE nurses will provide three-monthly three-day logs of their coaching activities of care staff members regarding specific clinical situations involving residents (who initiated the coaching activity, who participated, topic, form, duration, location). An outsider (etic) perspective will be obtained via go-along observations of INTERCARE nurses’ daily routines and coaching practices, conducted by a PhD student/research assistant for one working day (5–7 hours) per nurse, approximately six months after intervention start [67, 68]. Observations and informal conversations will be documented in Rapid Assessment Procedure (RAP) sheets [69].

### Data analysis

All quantitative data will be analyzed using R 4.5.x [70]. Descriptive statistics will summarize implementation, economic, and effectiveness outcomes and sample characteristics (means and standard deviations or medians and interquartile ranges for continuous variables, and frequencies and percentages for categorical variables). Multiple imputation will be considered depending on the extent of missing data [71]. Following CONSORT for cluster-RCTs [51], baseline differences between arms at the LTCF level will be presented using standardized mean differences and, where appropriate, frequencies and percentages.

For aim 1 (fidelity) and aim 2.1 (acceptability and feasibility), the non-inferiority margin is set at 15%. The non-inferiority of collaborative versus individualized support will be tested using binomial generalized linear mixed models with a random effect for LTCFs, and 95% confidence intervals; non-inferiority is confirmed if the lower confidence bound does not cross 15% below the arm II value.

A convergent mixed-methods approach will be used for aim 2.1. Qualitative data (interview notes, coaching activities reports, RAP sheets) will be analyzed using framework analysis [72, 73]. combining inductive and deductive themes to identify patterns in INTERCARE nurses’ practices and coaching approaches in acute situations. Qualitative findings will be compared with quantitative fidelity trajectories to explore fidelity moderators, and observational data will be coded in MAXQDA (https://www.maxqda.com/).

For aim 2.2, descriptive analyses will summarize intervention, implementation, and hospitalization costs by arm. A cost-effectiveness analysis will estimate the ICER, defined as the difference in costs between the two modes of delivery divided by the difference in their effects, measured as the number of unplanned hospital transfers. CEA helps identify ways to redirect resources to more cost-effective approaches [74]. We will use a multi-stakeholder perspective (i.e., LTCF and research group perspectives) and a 12-month time horizon, respecting the NICE guideline while reflecting data availability [75]. One-way sensitivity analysis and scenario analysis will be used to gauge our predictions’ level of uncertainty.

For aims 2.3a and 2.3b, the effects of the two delivery modes on unplanned transfers and staff outcomes will be analyzed using mixed-effects models analogous to those for aim 2.1, accounting for clustering at LTCF level.

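### The binomial model and 15% margin set for fidelity are also applied to acceptability and feasibility (AIM, FIM), with no event defined and no basis given for 15% on those outcomes

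*Protocol article*

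**What the plan says.** Three places in the protocol article bear on this.

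- **Data analysis.** The margin sentence covers several outcomes at once: "For aim 1 (fidelity) and aim 2.1 (acceptability and feasibility), the non-inferiority margin is set at 15" per cent. Non-inferiority is to be "tested using binomial generalized linear mixed models with a random effect for LTCFs, and 95% confidence intervals", and the decision rule is that "non-inferiority is confirmed if the lower confidence bound does not cross 15% below the arm II value".
- **Implementation outcomes (aims 1 and 2.1).** Fidelity is rated requirement by requirement, "yielding an overall fidelity score (percentage of minimal requirements implemented as intended) at each time point". For the other two outcomes the text names instruments only: "Acceptability and feasibility of selected core components will be assessed with the Acceptability of Intervention Measure (AIM) and Feasibility of Intervention Measure (FIM"). They are self-completed: "INTERCARE nurses and LTCF staff will complete online surveys at T0, as well as 6 and 12 months after intervention start (T2, T4"). Leadership is surveyed at T0 and T4 only. No response format, scoring or cut-off is given.
- **Sample size and inclusion criteria.** The 15% appears here for fidelity alone: "The sample size calculation assumes a 15% difference in overall fidelity between trial arms (65% vs. 80"%). The Abstract likewise states the margin for fidelity only.

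**The concern.** A binomial model needs an event and a denominator. A non-inferiority margin needs a scale and a reason why a loss of that size is acceptable on it. Fidelity has an event and a denominator, and its 15% ties to the sample size assumption. The Data analysis section carries the model, the margin and the decision rule over to acceptability and feasibility, for which the article supplies none of these elements.

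What is at stake is the credibility of two secondary non-inferiority statements. If AIM and FIM give a score per respondent, someone has to choose how to turn it into a proportion, and that choice sets how large a deficit on the score is tolerated. Allocation is open once a cohort is assigned and the surveys are self-reported, so the choice carries weight only if it is made before the responses are seen.

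**Working it through.** **1. The plan's own figures belong to fidelity.**
- ICC from the stated between-cluster variance: 0.1 / (0.1 + π²/3) = 0.0295, against the stated 0.029.
- Allowance for loss: 18 / (1 − 0.10) = 20 per arm, 40 in total, as stated.
- Power for 65% vs. 80% with 18 facilities per arm depends on the number of minimal requirements per facility, which the article does not give. In a simulation with a Wald test on facility proportions, facility effects of variance 0.1 on the logit scale and two-sided alpha 0.025, 13 requirements give 84%. For 60% vs. 80% the same setting gives 97%. Both match the stated figures, but 13 is an assumption.
- No equivalent check is possible for AIM or FIM, because event, denominator and expected rate are all absent.

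**2. The outcomes side by side.**

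| | Overall fidelity | Acceptability, feasibility |
|---|---|---|
| Source | Leadership interview, rated by researchers | Individual online surveys |
| Unit | One score per facility per time point | Many respondents per facility |
| Event | Requirement implemented as intended | Not stated |
| Denominator | Minimal requirements | Not stated |
| Basis for 15% | Sample size assumption, 65% vs. 80% | None stated |
| Model, margin, rule | Binomial, 15%, confidence bound | The same |

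Table 1 expects about 3,200 care staff in 40 facilities, so 3,200 / 40 = 80 per facility before non-response. If AIM and FIM were reduced to responder proportions, the denominator would be respondents, not requirements.

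**3. What 15 percentage points would mean on a score.** This takes only the reading that fits a binomial model. Everything here is assumed: a 1 to 5 mean score, approximately normal, with mean μ, SD σ and responder cut-off c.
- Responder proportion: p = 1 − Φ((c − μ)/σ).
- After a 15-point loss: q = p − 0.15.
- Implied mean: μ′ = c − σ·z(1 − q). Tolerated shift: μ − μ′.
- Example with μ = 4.0, σ = 0.8, c = 4.0: p = 0.50, q = 0.35, z(0.65) = 0.385, shift = 0.8 × 0.385 = 0.31.

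Tolerated shift in points, cut-off 3.5 / cut-off 4.0:

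| Mean | SD 0.6 | SD 0.8 | SD 1.0 |
|---|---|---|---|
| 3.5 | 0.23 / 0.47 | 0.31 / 0.46 | 0.39 / 0.50 |
| 4.0 | 0.27 / 0.23 | 0.33 / 0.31 | 0.40 / 0.39 |
| 4.5 | 0.49 / 0.27 | 0.47 / 0.33 | 0.50 / 0.40 |

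The range is 0.23 to 0.50 points. With mean and SD held fixed, moving the cut-off hardly matters at a mean of 4.0 but matters a good deal at 3.5 or 4.5 with SD 0.6. The cut-off is therefore part of the margin and has to be stated with it.

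**The case against.** The strongest reply is that this is a condensed article. Scoring rules for a secondary survey outcome normally sit in an analysis plan, and none is shown. Naming a binomial model already implies a proportion, such as the share of respondents who agree. The trial reduces a graded rating in just this way for fidelity, where a three-level classification becomes a percentage implemented as intended. The sample size section uses a 15% difference to mean 65% vs. 80%, so the margin reads most naturally as percentage points.

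Much of that stands, and it rules out several stronger readings.
- A reader might infer that the test cannot be applied to AIM and FIM at all. The article does not support this: with a defined responder proportion the rule would work.
- A reader might take it as established that AIM and FIM are rating-scale scores. The article gives only their names, respondents and timing.
- A reader might count 15% of a mean, a maximum or a scale range as live meanings of the margin. Those do not fit a binomial model.
- A reader might infer that a cut-off will be chosen after seeing the data. Nothing says so; an unseen plan may already fix it.

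The reply does not dispose of the point. The article did not leave this analysis open: it fixed the distribution, the margin and the decision rule. Having done so, it gives no event for the model to count, and a basis for 15% only on a different outcome. Percentage points may be the natural reading, but that does not show that 15 of them is a tolerable loss of acceptability or feasibility.

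**Conclusion.** The point holds in a limited form. For acceptability and feasibility the article commits to a binomial non-inferiority analysis with fidelity's margin, without saying what is counted or why 15% is acceptable there. That gap does not depend on how the instruments are scored. The further criticism, that a binomial model suits these outcomes poorly and loses information through dichotomising, rests on the assumption that each respondent yields a score.

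The size cannot be fixed from the article. The 0.23 to 0.50 point range is an illustration on an assumed 1 to 5 scale, not an estimate for this trial.

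The consequence is confined to two secondary outcomes under aim 2.1. It would be wrong to infer that the primary fidelity comparison or the sample size is undermined: both use an outcome with a defined proportion. This is worth correcting, but it does not threaten the trial.

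**What to change.** **Preferred.** Take acceptability and feasibility out of the sentence that sets the binomial model and the 15% margin. Analyse the T4 AIM and FIM scores with a linear mixed model with a random facility effect and the facility's mean score at T0 as covariate, and report the difference between arms with a 95% confidence interval. Claim non-inferiority only against a margin stated in advance in scale points. The T0 surveys are already scheduled in Table 2 for all the groups that complete the instruments.

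**If the binomial model is kept.** State the responder cut-off before any responses are examined, define the proportion and its denominator, and give the margin as 15 percentage points on that proportion with a justification separate from fidelity's.

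**Cost.** One or two sentences of analysis text and no new data. A margin specific to the instrument has to be justified; if it cannot be, the non-inferiority claim is dropped and the difference is reported as an estimate. The models for transfers and staff outcomes are described by reference to aim 2.1, so that cross-reference needs checking when the text changes.
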